### Additional analyses

Additional analyses will take place for the individual endpoints, which are combined into the aggregate endpoint of emergence contacts. Subgroup analyses as well as sensitivity analyses will be performed.

### Analysis population and missing data

The data for the analyses come from different sources. The data of the control group and the data of the insured persons of the participating health insurers are assumed to be complete. Data from the ASHIP are available for all patients. Therefore, it can be assumed that the outpatient care data of all patients are complete. Inpatient data of patients who are not insured by the participating health insurance company will be requested from the APN and entered into a database. Subgroup analyses were performed to assess the data quality of these data. Data can be supplemented by means of imputation procedures.

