### Outcomes

#### Primary endpoint

The primary endpoint is the number of emergency contacts per patient within one year. Emergency contacts are visits to the on-call medical service, GP contacts outside office hours and unplanned hospital admissions.

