### Participant timeline

The initial data of the participating patients includes age, sex, medical diagnoses, and number and duration of illnesses. These data are collected during the enrolment phase. Each patient enrolled in the project takes part in APN care for twelve months. The initial assessment lasts on average 1.5 hours. Follow-up contacts for the implementation and continuation of the care plan usually take place every four weeks. Depending on the need, however, the intervals can also be significantly shorter or significantly longer. APN contact is held at least quarterly. Routine contacts last on average 30 minutes. Depending on patient concerns and needs, the time frame may vary.

Routine data are used to count emergency contacts as the primary outcome measure, which means that there is no time stress for the patients. Secondary data are supplied by the ASHIP and by one health insurance company. However, there are patients for whom not all data regarding hospital and emergency contacts are available from routine data. For them, data are collected by the APNs. These data are also used for the analysis of secondary endpoints and health economic analyses. In addition, 30 patients will be interviewed about their experiences after completion of the 12-month intervention. We do not foresee the need for follow-up data collection.

The assessment tools mentioned above are used to measure the health status of the patients in the internal assessment. Data will be collected at the beginning (t0) and at the end (t1) of the 12-month intervention. Patient satisfaction with APN care is measured using a project-specific questionnaire.

The participants’ timeline in relation to the individual steps that occur during enrolment, intervention and evaluation is shown in Table 2:

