## Methods: data collection, management, analysis

### Data collection methods

For the independent evaluation, data from ASHIP and the health insurance fund will be used for primary and secondary endpoints. To fill in missing data, such as hospital visits for patients with other health insurance, APNs collect health-related data and document patients' emergency and routine visits to any health-related facility (doctor's office, hospital, emergency room). The health insurer provides a data pool for control group matching. All data are transferred to the IMBEI in pseudonymized form. Patients, GPs, and APNs are informed by mailed invitations about the possibility of interview participation and asked to complete a feedback form. Potential interviewees are called via the feedback form, and appointments are made. The qualitative interviews are conducted by telephone using a previously prepared standardized interview guide. There is a separate guide for each interview group, which is finalized after piloting. Interviews are audio recorded and transcribed verbatim.

As part of the internal evaluation, the health status of each participating patient was measured before (t0) and at the end of the patient-individual intervention phase (t1) using the assessment instruments mentioned in the intervention section above as we use the data from these instruments for care and research purposes. Their psychometric data are as follows: DemTect: interrater reliability *r* = 0.993, sensitivity 85.1%, specificity 97% [14]; MNA: internal consistency α = 0.701, test–retest reliability *r* = 0.697 [23]; NRS: with a cut-off point NRS > 4, the sensitivity of ‘unbearable pain’ is 83%, while the specificity is 96.7%, with a cut-off point NRS > 5, the sensitivity is 94%, while the specificity is 85% [24]; PDI: internal consistency α = 0.86, [17]; HAQ: internal consistency α = 0.78–0.98 [25, 26]. The psychometric results of the German translation are as follows: test–retest reliability 0.94, internal consistency α = 0.92, criterion validity 0.76 [27]; MILVA: internal consistency range between α = 0.61–0.94, sensitivity 72%, specificity 59%; [17]. PAINAD-G: internal consistency α = 0.85, interrater stability *r* = 0.80, retest reliability* r* = 0.90 [21]; DEMMI: internal consistency α = 0.83, interrater reliability ICC 0.94 [28].

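### For intervention patients of other insurers, unplanned admissions come only from the APN's records, while controls have them from insurer data, so under-recording would lower the primary endpoint in one arm only

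*Protocol article*

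**What the plan says.** The Primary endpoint section defines the composite: "Emergency contacts are visits to the on-call medical service, GP contacts outside office hours and unplanned hospital admissions". It is counted per patient over one year.

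The sources differ by arm and by insurer:

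- **Controls.** Under Data collection methods, "The health insurer provides a data pool for control group matching". Under Analysis population and missing data, "The data of the control group and the data of the insured persons of the participating health insurers are assumed to be complete".
- **Outpatient components.** The latter section also says "Data from the ASHIP are available for all patients" and infers that outpatient data are complete.
- **Admissions, intervention patients of other insurers.** "Inpatient data of patients who are not insured by the participating health insurance company will be requested from the APN". Data collection methods agrees: "To fill in missing data, such as hospital visits for patients with other health insurance, APNs collect health-related data".

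Eligibility is open to patients of any statutory insurer, while Participant timeline names a single insurer as data supplier. That section also says "there are patients for whom not all data regarding hospital and emergency contacts are available from routine data", and that the APN collects the data for those patients. The Interventions section has the APN taking over the patients' care, and the study is nonblinded.

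The stated safeguards are these: "Subgroup analyses were performed to assess the data quality of these data"; a remark that imputation may be used; and, under Additional analyses, separate analyses of the endpoint components plus subgroup and sensitivity analyses whose content is not given. The primary analysis is a pooled Poisson regression.

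**The concern.** One component of the primary endpoint is measured differently in the two arms. In controls an admission is counted because it was billed. In an intervention patient of another insurer it is counted only if the APN hears of it and enters it. On the plan's own assumption of complete control data, controls suffer no matching loss, so each missed admission appears as a benefit of APN care.

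The safeguards do not repair this. A subgroup check of data quality describes the data and leaves the pooled estimate unchanged. Imputation needs a recognised gap, and an admission nobody reported looks like no admission. A reduction in the pooled composite could therefore not be fully separated from incomplete recording.

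The problem extends beyond the composite. APN-collected data also feed the secondary endpoints, which include hospitalisation and readmission. When admissions are analysed alone, no outpatient contacts dilute the artefact.

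**Working it through.** **Plan's figures.** The sample size section gives 2.7 contacts per patient-year and a 15% reduction: 2.7 × 0.85 = 2.295, a difference of 0.405. This reproduces. The totals of 817 and 1634 cannot be reproduced because the cluster effect is not quantified. They are used here only as patient numbers. After 30% dropout: 817 × 0.7 ≈ 572 and 1634 × 0.7 ≈ 1144.

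**Size of the artefact.** Let *a* be the share of emergency contacts that are unplanned admissions, *s* the share of intervention patients with another insurer, and *u* the share of those patients' admissions that go unrecorded. With no true effect and the same admission rate across insurers, the apparent rate ratio is 1 − *a·s·u*. The protocol gives none of the three, so all values below are assumptions.

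| Case | a | s | u | Spurious reduction | Share of 15% target |
|---|---|---|---|---|---|
| Low | 0.20 | 0.40 | 0.10 | 0.8% | 5% |
| Central | 0.30 | 0.60 | 0.20 | 3.6% | 24% |
| High | 0.50 | 0.80 | 0.30 | 12% | 80% |

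The central case is 2.7 × 0.036 = 0.097 contacts per patient-year, against the planned 0.405. The high case sets all three inputs at their upper limits together.

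**Admissions analysed alone.** The factor *a* drops out, leaving *s·u*: 0.4 × 0.1 = 4% (low), 0.6 × 0.2 = 12% (central), 0.8 × 0.3 = 24% (high).

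**Effect on the test.** Take the central case with no true effect and 572/1144 patients. Under Poisson variance the SE of the log rate ratio is √[1/(572 × 2.7 × 0.964) + 1/(1144 × 2.7)] = 0.0316, and ln 0.964 = −0.0367. The shift is 0.0367/0.0316 = 1.16 standard errors, which gives a two-sided false-positive rate of about 21% instead of 5%. With greater variance the shift matters less: a 4% artefact gives about 25% under Poisson variance and 11% at 3.5 times that variance.

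**Precision of a claims-in-both-arms comparison.** Assume the participating insurer covers 40% of patients: 572 × 0.4 ≈ 229 and 1144 × 0.4 ≈ 458. With nine practices, cluster size falls from about 63.6 to 25.4. The variance of the rate difference, with only the intervention arm clustered, is 2.295 × DE/n₁ + 2.7/n₀, where DE = 1 + (m − 1) × ICC.

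| ICC (assumed) | DE full / subset | Variance full / subset | SE ratio |
|---|---|---|---|
| 0.058 | 4.62 / 2.41 | 0.0209 / 0.0301 | 1.20 |
| 0.03 | 2.88 / 1.73 | 0.0139 / 0.0233 | 1.29 |
| Unclustered, as the analysis is planned | – | – | √(1/0.4) = 1.58 |

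The ICC of 0.058 gives 80% power at 572/1144 when only the intervention arm is clustered. The ICC of 0.03 lies within the 0.023 to 0.036 needed to reach 817 if the design effect is applied to the whole two-sided calculation. At ICC 0.058 the subset's power is about 65% (0.405/√0.0301 − 1.96 = 0.37).

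**The case against.** **Under-recording is not certain.** Participant timeline sets quarterly contact only as the minimum; visits are usually four-weekly. APNs and GPs hold weekly case conferences, mentors monitor the documentation form continuously, and IMBEI checks APN entries for plausibility. All of this makes a missed admission less likely, though none of it is a check against claims. This stands, and a reader should not infer that the bias is known to be present or large.

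**Direction is not guaranteed.** APNs document emergency and routine visits to any health facility, which is wider than the endpoint. A planned admission entered as unplanned would raise the intervention count.

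**Additional analyses help in part.** Analysing components separately keeps the outpatient components apart, and these come from ASHIP data for everyone. A same-insurer comparison could also be one of the sensitivity analyses left to the analysis plan. But the component analysis shows the admission result without correcting it, and no section ties the main conclusion to a same-source result.

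**Stronger readings that the text does not support.** A reader might infer that APN capture can never be measured because no patient has both sources. Participant timeline points that way, but Data collection methods gives patients of other insurers only as an example, and Data management has APNs entering intervention-group data without limit by insurer. The text is ambiguous. A reader might also infer that comorbidity for matching comes from different sources in the two arms. No section states the source in either arm.

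**Conclusion.** The asymmetry is explicit and touches a primary-endpoint component. If APNs under-record, the composite falls in the intervention arm only, in the direction of the hypothesis, and nothing planned corrects the pooled estimate.

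The size is unknown. The range of 0.8% to 12%, with 3.6% as the central case, rests on three assumed inputs and on complete control data, which is the protocol's assumption and not a demonstrated fact. It also takes ASHIP outpatient data to be complete, as Analysis population and missing data says. Participant timeline suggests that emergency contacts too may be absent from routine data for some patients. If so, the exposure is wider.

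This is an inexpensive improvement that changes what the trial can conclude. It does not show that the primary analysis is invalid. Nor does it follow that the same-source comparison should replace the primary analysis: the loss of precision makes that a debatable trade.

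**What to change.** 1. Reconcile Participant timeline, Data collection methods, and Analysis population and missing data on which patients and which contacts the APN records. Have APNs record hospital and emergency contacts for all intervention patients, including those of the participating insurer. Estimate APN capture against claims in that insurer's patients and report it beside the primary result.

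2. Pre-specify a same-source comparison as a required companion to the pooled primary analysis: intervention patients of the participating insurer against their own matched controls, with claims in both arms. Claim a reduction only if the two estimates are consistent. Define consistency beforehand in terms of the estimates and their intervals, not as significance of the companion.

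**Cost.** A little more documentation by APNs who already record contacts, and some analysis-plan wording. The companion is less precise: if the insurer covers 40% of patients, its SE rises by about 20% to 30% with a clustered intervention arm and by about 58% under the planned unclustered Poisson model. That is why it should accompany the primary analysis and not replace it.

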## Monitoring methods

### Data monitoring

Due to the low risk, no data monitoring committee (DMC) will be established. Interim analyses will not be conducted.

### Harms

Adverse events are not to be expected. APNs will be in regular contact with patients, so they should be able to detect any deterioration in their health status. If the APNs notice any unclear change in the health status of the patients, they will discuss this with the GPs. In addition, the GPs have regular contact with the patients. If any adverse event should occur, the APN will report to the mentor accompanying her or him.

### Auditing

The routine data provided by the health insurance company and ASHIP are controlled and quality-checked through well-established procedures. These high control standards are necessary beyond the research requirements because routine data are usually the basis for billing modalities.

The documentation form, which is used to document the patients' health status and the activities of the APNs, is continuously monitored by the experienced mentors who accompany the APNs. In the monthly structured evaluation meetings or - if necessary - in between, the mentors provide the APNs with feedback and discuss any need for improvement.

Mentors are part of the project team, which holds weekly meetings to discuss the progress of the project and to make steering decisions as necessary.

## Ethics and dissemination

### Research ethics approval

The protocol, informed consent forms, participant education and recruitment materials, and other requested documents were approved by the Ethics Committee of the German Society of Nursing Science. The ethical reference issued (No. 21–012). All methods were carried out in accordance with relevant guidelines and regulations. Informed consent was obtained from all subjects or their legal guardian.

### Protocol amendments

Any change to the protocol that may affect the conduct of the study, potential benefit to patients, or patient safety, including changes in study objectives, study design, patient population, sample size, study procedures, or significant administrative aspects, will require a formal amendment to the protocol. Such a change will be submitted to the Ethics Committee of the German Society for Nursing Science and will only be implemented if approved.

Administrative changes to the protocol are minor corrections and/or clarifications that do not affect the conduct of the study. The Ethics Committee of the German Society for Nursing Science will be informed about these administrative changes.

### Consent or assent

Patients who meet the inclusion criteria are informed verbally and in writing by their GP. If desired, patients will have the opportunity to speak with their potential future APN. She or he will explain the APN care program again. General practitioners obtained informed consent from patients if they decided to participate in the study. Participants document their informed consent by signing a treatment contract. If necessary, the information is passed on to the legal representatives, and their signature on the treatment contract is obtained.

### Confidentiality

In accordance with the GDPR and the project-specific data privacy concept, all study-related information is kept securely at the study site. All participant information is kept in locked file cabinets. All reports, data collection, process, and administrative forms will be marked with a coded ID (identification number) only to maintain participant confidentiality. All records containing names or other personal identifiers, such as consent forms, are kept separate from study records, which are marked with a code number. All local databases are secured by a password protected access system. The health record consists of two parts: part one contains the data identifying the person, and part two contains the health-related data. The person-identifying data and the health-related data are hosted on different servers. Therefore, only pseudonymized data are made available to the external evaluator.

### Access to data

The Principal Investigator will have access to the cleaned datasets by the independent evaluator. All other partners involved in the project may have access to the data upon request. There are no contractual agreements restricting this access.

### Ancillary and posttrial care

During the intervention phase, care is provided by the APN within the framework of delegation. This means that the physicians are informed at all times about the patient's state of health and the treatment steps. After the end of the intervention, the patients returned to the normal care of general practice.

### Dissemination policy

The study group aims to publish the results in scientific papers, present them at scientific congresses and use all appropriate channels from a scientific point of view to inform the scientific community. In addition, the study group will inform policy-makers and health care providers involved in this area about the outcomes. The various partners of the study group will be informed in advance of planned publications as contractually agreed upon.

The main publication will be prepared by the study director. All active project partners are coauthors, according to the guidelines of the ICMJE [30].

All partners involved in the project are allowed to publish the data obtained. To do so, they must first prepare an exposé that is submitted to the Publication Steering Committee, which is composed of the study director and the head of the independent evaluation. If the exposé is approved, an application for data export can then be submitted to the IMBEI. All publications must be submitted to and approved by the FAMOUS Publication Steering Committee prior to submission.

## Data Availability

Under the assumption that national data protection requirements are fully met, access to aggregated or pseudonymized individual-level data may be made available upon reasonable request. All data access requests should be directed to the corresponding author.

## Abbreviations

APN: Advanced Practice Nurse
APN-BQ: Advanced Practice Nurse- counselling quality [Beratungsqualität]
ASHIP: Association of Statutory Health Insurance Physicians
CUAS: Catholic University of Applied Sciences
DEMMI: De Morton Mobility Index
DemTect: Dementia Detection
DMC: Data Monitoring Committee
DRKS: German Clinical Trials Register [Deutsches Register Klinischer Studien]
FAMOUS: Case-based care of multimorbid patients in general practice by advanced practice nurses [Fallbezogene Versorgung multimorbider Patient/innen in der Hausarztpraxis durch Advanced Practice Nurses]
GDPR: General Data Protection Regulation
GP: General Practitioner
HAQ: Health Assessment Questionnaire
ICC: Intra-Class Correlation coefficient
ICMJE: International Committee of Medical Journal Editors
IMBEI: Institute of Medical Biostatistics, Epidemiology and Informatics
IZKS: Interdisciplinary Center Clinical Trials
MILVA: Mannheim Inventory of Living Conditions in Old Age [Mannheimer Inventar der Lebensverhältnisse im Alter]
MNA: Mini Nutritional Assessment
n/a: Not applicable
NRS: Numeric Rating Scale
PAINAD-G: Pain Assessment in Advanced Dementia Scale
PDI: Pain Disability Index
SHI: Statutory Health Insurance
